### Sample size

To develop a prognostic prediction model, the required sample size may be determined by three criteria suggested by Riley *et al*.^30^ For example, suppose a maximum of 200 parameters will be included in the prediction model and the Cox-Snell generalised R^2^ is assumed to be 0.01. A total of 377 996 patients will be required to meet Riley’s criterion (1) with global shrinkage factor of 0.95; this sample size also ensures a small absolute difference (Δ<0.05) in the apparent and adjusted Nagelkerke R^2^ (Riley’s criterion (2)) and ensures precise estimate of overall risk with a margin of error <0.001 (Riley’s criterion (3)). According to the Quality and Outcomes Framework, the prevalence of AF in England is 1.7%.^31 32^ Given an AF prevalence of 1.7%, only 6425 patients will be expected to develop AF from 377 996 patients. Therefore, the number of patients in the CPRD dataset with AF will provide sufficient statistical power to develop and validate a deep learning prediction algorithm with the predefined precision and accuracy.

### Predictor variables

A systematic review has highlighted 22 predictor variables included in varying combinations by 10 preceding prediction models developed to detect incident AF in the community.^16^ In addition, a more recently published machine learning model has established six further time-varying variables (eg, change in body mass index between the latest two quarters).^19^

To capture the full potential of deep learning and this large dataset, we will broaden our search for candidate predictors to all available variables, while retaining temporal information (including all clinical assessments, hospitalised events and medications). The potential predictors may include the following:

Sociodemographic variables including age, sex, ethnicity and indices of multiple deprivation.All disease conditions during follow-up, including hospitalised diseases and procedures, such as other cardiovascular diseases, diabetes mellitus, chronic lung disease, renal disease, inflammatory disease, cancer, hypothyroidism and surgical procedures.Clinical assessments including heart rate, systolic and diastolic blood pressure, height, weight and body mass index.Medications prescribed including antihypertensives, statins, antidepressants, anxiolytics/hypnotics and antipsychotics.Lifestyle factors including smoking status and alcohol consumption.All biomarkers routinely collected during follow-up including total, high-density lipoprotein and low-density lipoprotein cholesterol, triglycerides, creatinine, C reactive protein, erythrocyte sedimentation rate.

Predictive factors will be identified using the appropriate codes. In CPRD, we will use Read codes for diagnoses, measurements (eg, systolic and diastolic values) and product codes (prodcodes) for medications. In HES APC, we will use ICD-10 codes and Office of Population Censuses and Surveys Classification of Interventions and Procedures version 4 (OPCS-4) codes. In the ONS Death Registration data file, we will use ICD-10 codes (and ICD-9 codes for the period before 2001).

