**Methods and analysis:**

We will investigate the application of a range of deep learning techniques, including an adapted convolutional neural network, recurrent neural network and Transformer, on routinely collected primary care data to create a personalised model predicting the risk of new-onset AF over a range of time periods. The Clinical Practice Research Datalink (CPRD)-GOLD dataset will be used for derivation, and the CPRD-AURUM dataset will be used for external geographical validation. Both comprise a sizeable representative population and are linked at patient-level to secondary care databases. The performance of the deep learning models will be compared against classic machine learning and traditional statistical predictive modelling methods. We will only use risk factors accessible in primary care and endow the model with the ability to update risk prediction as it is presented with new data, to make the model more useful in clinical practice.

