To date, several multivariable prediction models have been created or tested for prediction of incident AF in the community. The earliest models were derived from structured follow-up of prospective cohorts, including Framingham Heart Study score for Atrial Fibrillation and CHARGE-AF (Cohorts for Heart and Ageing Research in Genomic Epidemiology for Atrial Fibrillation).^12 13^ The proliferation of electronic health records (EHRs) has led to the development of several models from local registries, including Maccabi Healthcare Services and C_2_HEST (Coronary artery disease/chronic obstructive pulmonary disease, Hypertension, Elderly, Systolic heart failure, Thyroid disease).^14 15^ Structured EHRs offer larger sample sizes to assess more candidate variables and derive more generalisable models.

A systematic review found that the models derived from prospective cohorts had been more frequently externally validated. CHARGE-AF was the only model that showed significant overall discrimination in meta-analysis but its transportability to EHRs is still being investigated.^16 17^ Each model to date is, however, limited by one or more of their use of small, geographically remote or historical datasets, lack of temporal information, crude risk modelling with consequent suboptimal model performance and/or predictor variables not readily available in primary care.^18^ None has yet reached widespread clinical practice.

Machine learning is a data-driven approach that can identify non-linear associations and complex interactions between variables without the need to specify these relationships *a priori*.^19^ A recent study applying this methodology to a nationwide UK dataset produced a model with a greater discriminative capability than CHARGE-AF (area under receiver operating characteristic (AUC) 0.827 vs 0.725) in EHR.^19^

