### Research aim

The aims of the Future Innovations in Novel Detection of Atrial Fibrillation (FIND-AF) study are to:

Develop a deep learning model for predicting the risk, *and evolution of the risk,* of new-onset AF in primary care.Identify and quantify the magnitude of risk markers of new AF among routinely collected primary care data.Externally validate the model in a geographically distinct dataset to assess generalisability.

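### Predictor sources go beyond the primary care limit set in the abstract, include death records that cannot validly predict AF, and are worded so that inputs dated after the diagnosis are allowed

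*Protocol article*

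**What the plan says.** Three places in the protocol article tie the model to primary care data:

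- Abstract, Methods and analysis: "We will only use risk factors accessible in primary care". This is given as a reason why the model will be useful in practice.
- Research aim: "Identify and quantify the magnitude of risk markers of new AF among routinely collected primary care data".
- Introduction, listing weaknesses of earlier models: "predictor variables not readily available in primary care".

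Ethics and dissemination adds that the algorithm could be built into general practice systems.

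The Predictor variables section goes wider. On scope: "we will broaden our search for candidate predictors to all available variables, while retaining temporal information (including all clinical assessments, hospitalised events and medications". On timing: "All disease conditions during follow-up, including hospitalised diseases and procedures" and "All biomarkers routinely collected during follow-up". On sources, after Read and product codes for the GP data, it adds "In HES APC, we will use ICD-10 codes and Office of Population Censuses and Surveys Classification of Interventions and Procedures version 4" and then "In the ONS Death Registration data file, we will use ICD-10 codes (and ICD-9 codes for the period before 2001".

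Outcome ascertainment sets the baseline at 1 January 2009 and counts first AF or atrial flutter after it. The outcome is found in the GP record, HES APC and the underlying cause of death from ONS Death Registration.

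**The concern.** The limit in the Abstract and the sources in Predictor variables do not agree. The sentence on death records stands among the rules for identifying predictors. Outcome ascertainment has its own section, so as written the death register is a source of model inputs. The hospital sources are linked data that a tool inside a practice system would not hold in that form. The two bullets that refer to follow-up give no end date for an input, although AF is counted over part of the same period.

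What is at stake is the meaning of the reported discrimination and calibration. If the models are fitted and tested with linked hospital data, the results describe performance with that linkage, whereas the stated use is on GP records. If codes entered at or after an AF diagnosis become inputs, performance is overstated. Success is defined in Ethics and dissemination as a gain of at least 5% in predictive accuracy over existing models, so an optimistic estimate bears directly on that judgement.

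**Working it through.** No figure stated in the protocol depends on this point, and the sample size is unaffected. The check sets sections and dates side by side.

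**1. Are hospital and death codes really model inputs?** The list of potential predictors is tentative, but the sentences on code sources are not: they state what will be used. Development and external validation of model then says that Read and ICD codes will both be mapped to Caliber categories during preprocessing. Elsewhere the protocol names ICD codes only for HES and ONS, and Read or SNOMED codes for the GP data. So ICD-coded data are meant to enter the models.

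**2. Can a death record be a predictor?** The inputs are the baseline of 1 January 2009 (Outcome ascertainment) and the use of ICD-9 for deaths before 2001 (Predictor variables).

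- Death coded in ICD-9, on 31 December 2000 at the latest: from then to 1 January 2009 is 2,923 days, and 2,923 / 365.25 = 8.0 years. The person died at least 8 years before baseline and is never at risk of the outcome.
- Death from 2001 up to baseline: the person is again not at risk.
- Death after baseline: the record comes into being only when the person's time at risk has ended, so it cannot precede AF in that person.
- If the underlying cause is AF or flutter, the record is itself an outcome event under Outcome ascertainment.

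No period remains in which a cause-of-death code is a usable predictor.

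**3. What does follow-up span?** Inclusion and exclusion criteria uses the term for time between 2 January 1998 and 30 November 2018.

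| Interval | Days | Years (days / 365.25) |
|---|---|---|
| 2 January 1998 to 1 January 2009 | 4,017 | 11.0 |
| 1 January 2009 to 30 November 2018 | 3,620 | 9.9 |
| Whole window | 7,637 | 20.9 |

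About 9.9 of 20.9 years (47%) lie after baseline, in the time when AF is counted. The article gives no rule that stops inputs at the prediction date or before the AF diagnosis. Missing data limits baseline information to measures from the last year, but its examples are smoking, cholesterol, blood pressure and weight. It does not bound the event sequences that feed the neural networks.

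**4. Would external validation show the problem?** Data sources and permissions applies the same linkage (HES, ONS and deprivation) to the patients extracted from both datasets. A model that relies on hospital-coded inputs would find them in AURUM too. The validation tests transfer to other practices, not transfer to GP records without linkage.

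**The case against.** The best defence has four parts.

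*Access is not source.* The Abstract speaks of factors that primary care can access, and just before that says the data are linked to secondary care. Conditions such as diabetes, renal disease or cancer are usually in the GP record as well. Because Read and ICD codes go to common Caliber categories, a feature built partly from HES could be filled from Read codes alone. This stands to a good extent. A reader might infer that the model could not be run in general practice at all. The documents do not support that: what may differ is the completeness of the features, and with it the performance. The defence does not remove the gap, since the sources sentence also names OPCS-4 procedure codes and the section on mapping mentions only Read, ICD and product codes.

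*Follow-up includes the years before baseline.* A model meant to update risk may properly use data after 2009 up to each prediction date. This stands. A reader might infer that data from after the outcome will be used. The text does not prescribe that; it only fails to exclude it.

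*A condensed article leaves exact windows to the full protocol.* This is fair for the details of windows. It does not cover wording that is in print and spans both sides of baseline.

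*The death-records sentence may be an outcome code list in the wrong place.* That is plausible, since Outcome ascertainment already uses the file. It would make the repair easy, but the sentence as printed still names a predictor source. A reader might also say that all death-register features lie after baseline. The pre-2001 ICD-9 codes contradict this; the sound argument is that neither earlier nor later deaths can predict.

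**Conclusion.** The contradiction is real and should be resolved before models are fitted. Its parts differ in strength.

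- **Death registration:** wrong as written. No death record can validly predict AF in a person at risk, whatever its date. This rests only on the protocol's own baseline and outcome definition.
- **Hospital sources:** in conflict with the limit in the Abstract. The practical effect is that performance estimated with linked data may not be reproduced from GP records alone, and AURUM would not reveal it. How much is lost depends on how completely hospital diagnoses reach the GP record, which the protocol does not say.
- **Timing:** the wording permits inputs dated at or after AF but does not require them. If they entered, the bias in performance would be upward. Its size cannot be derived from the document, and none is claimed here.

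**What to change.** 1. Delete ONS Death Registration from the identification of predictors. Use it only for the outcome and for censoring at death.
2. In the bullets on disease conditions and biomarkers, replace the reference to follow-up with: recorded on or before the prediction date and before any AF/AFl diagnosis. This still allows a model that updates over time.
3. Make the primary model one that uses GP-record inputs only, and report its performance in both GOLD and AURUM. Any model with HES inputs is labelled secondary. State whether the linked deprivation indices count as available to the practice.
4. If the investigators prefer to keep HES inputs in the primary model, amend the promise in the Abstract and also report performance with GP-record inputs only.

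The cost is some rewording, fewer inputs and possibly a somewhat lower reported AUC. HES stays in use for finding the outcome.

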### Missing data

Missing data are expected in EHR data, and will be handled using multiple imputations according to the approaches suggested by Carpenter and Kenward, and depending on the amount of missing data.^33^ It is likely there will be misclassification of baseline characteristics, such as smoking status, cholesterol, blood pressure and weight that change over time. To account for this, we will define baseline information using only measures recorded within the last year. We will then use measures taken within the last 2–5 years and in the year after baseline as parameters in the chained imputation equations used to impute baseline covariates with ≤40% missingness. In addition, median imputation, a common approach to deal with missing values in machine learning algorithms, will be used to test the model robustness.^34^

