### Data analysis plan

#### Development and external validation of model

The CPRD-GOLD and CPRD-AURUM data will be cleaned and preprocessed for model development and validation, respectively. Specifically, for patient features with binary values, 0 and 1 will be mapped to the binary values. Variables with multiple categories will be split into their component categories, and each given a binary value to indicate the presence or not of the variable for each patient. Continuous variables will be kept as continuous. To reduce the high cardinality of Read codes and ICD codes, we will map both to Caliber codes,^35^ which is an expert checked mapping directory from University College London. Prodcodes can be mapped to level 2 of British National Formulary codes.^36^

A number of deep learning models will be investigated for prediction of AF in CPRD-GOLD. These will include a convolutional neural network (CNN), a recurrent neural network (RNN) and a Transformer architecture. They each possess characteristics that can capture the temporality of EHR data and the progression of a patient’s health status.

Although CNNs are typically associated with static content (eg, images and documents), they are increasingly used to uncover temporal relationships in EHR.^37–40^ The patient EHR can be converted to a temporal matrix, with one dimension corresponding to time and the other dimension corresponding to medical events (figure 1A).^37^ A one-sided convolution operation can be applied to each possible window of features in the event matrix to produce a feature map followed with max pooling (to capture the most important features) and culminating in a fully connected layer and softmax classifier. If the time dimension is embedded in 1-day increments, we have the option to learn temporal features by extending connectivity in the time dimension through a range of fusion strategies. Temporal early fusion could combine information across an entire time window to establish global patterns, temporal late fusion can be performed in the fully connected layer to model local connections and temporal slow fusion could capture both by extending the connectivity of all convolutional layers.^37^

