Finally, Transformers have become state of the art in natural language processing,^53 54^ and we will apply an adaption for EHR, BEHRT (BERT [Bidirectional Encoder Representations from Transformers] for EHR), which was originally developed in CPRD.^55^ This model’s structure, depicting each diagnosis code as a word, with each visit as a sentence and the entire medical history as a document, facilitates multihead self-attention, positional encoding and masked language model for EHR. BEHRT can define a representation incorporating information on the diseases afflicting a patient, the positional interactions of diseases and sequence of events, with the age of a patient linked to each visit to give a sense of time between diagnoses.^55^ This representation can then be used for a number of tasks including disease prediction.

Preprocessed patient-level data in CPRD-GOLD will be randomly split into an 80:20 ratio to create training and testing samples. The split ratio is not a significant factor, given the volume of the sample size. The model parameters and dropout rate will be chosen through a grid search and 10-fold cross-validation will be used (ie, 10% of the training data will be randomly selected as the cross-validation set).

While the outcome is binary, instead of just predicting 0 or 1 for a patient (new AF or not), the probability of that patient developing AF by different time points over months (1, 3, 6) and years (1, 5, 10) may be predicted. The probability of developing AF at each time point could be plotted to give an understanding of evolving risk of AF. The clinical risk prediction performance of the deep learning models will be compared against a range of classic machine learning techniques and traditional statistical predictive modelling methods including support vector machine, random forest, naïve Bayes and Cox proportional hazards model. Discrimination (Harrell’s c-statistic and AUC) and calibration metrics will be supplemented with positive and negative predictive values, precision, recall and area under precision-recall curve for all models.

The CPRD-AURUM dataset will then externally validate the model performance to assess generalisability. It has been shown that a lack of external validation has hampered the implementation of previous machine learning models in routine clinical practice.^56^

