### Software

The deep learning model will be implemented in R (through the R studio interface) and TensorFlow or Python and PyTorch including data preprocessing, missing data imputation, model development and validation.

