### Ethics and dissemination

The study has been approved by CPRD (ref no: 19_076). Those handling data have completed University of Leeds information security training. All analyses will be conducted in concordance with the CPRD study dataset agreement between the Secretary of State for Health and Social Care and the University of Leeds.

The study is informed by the Prognosis Research Strategy (PROGRESS) framework and recommendations.^58^ The subsequent research paper will be submitted for publication in a peer-reviewed journal and will be written following Transparent Reporting of a multivariable prediction model for Individual Prognosis or Diagnosis (TRIPOD) and REporting of studies Conducted using Observational Routinely collected health Data (RECORD) guidelines.^59 60^

If the model succeeds (defined as improving predicting accuracy by at least 5% compared with existing models), the algorithm could be made readily available through free-to-use software. The model will be designed to be amenable to in situ updating with new information so that prediction of an individual’s AF risk is updated contemporaneously. The algorithm could be a built-in tool for use in general practices to ‘screen’ for patients at high risk of developing new-onset AF. Future research will be needed to assess the clinical impact of this risk model. At the point when utilisation in clinical practice is possible, the applicable regulation on medicine devices will be adhered to.^61^ When in clinical use, the model itself could also be reviewed and updated by a prespecified expert consensus group on an annual basis after incorporating evidence from post-service utilisation and the curation of more data.

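### Baseline covariates are imputed using measures from the year after baseline, so test and validation performance would not be that of a tool scoring a patient prospectively

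*Protocol article*

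**What the plan says.** The article's Missing data section opens: "Missing data are expected in EHR data, and will be handled using multiple imputations", with the approach depending on how much is missing. Baseline values are those recorded in the last year. Gaps are filled using measures from the previous 2–5 years and those taken "in the year after baseline as parameters in the chained imputation equations used to impute baseline covariates with ≤40% missingness". A second method is listed as a check: "median imputation, a common approach to deal with missing values in machine learning algorithms, will be used to test the model robustness".

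Under Outcome ascertainment, baseline is 1 January 2009 and the outcome is a first diagnosis of AF or atrial flutter after that date.

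Under Development and external validation of model, "Preprocessed patient-level data in CPRD-GOLD will be randomly split into an 80:20 ratio to create training and testing samples". Risk may be predicted at 1, 3 and 6 months and at 1, 5 and 10 years, and "The CPRD-AURUM dataset will then externally validate the model performance to assess generalisability".

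Under Ethics and dissemination, the intended use is conditional on success: "The algorithm could be a built-in tool for use in general practices", with an individual's risk updated as new information arrives.

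**The concern.** A prognostic model is judged on what it predicts from information held at the time of prediction. Here a missing baseline blood pressure, weight or cholesterol value may be filled from a measurement made up to a year later. If the patient developed AF in the meantime, that measurement may reflect the disease, its work-up or its treatment. Even if it does not, it tells the model something about the baseline value that a prospective user would not know.

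In the training data this is a question of efficiency. In the data used for evaluation it makes discrimination look better than a practice could obtain. External validation does not remove the problem if AURUM is imputed in the same way, because the later measures would enter there too. The figures at stake are those by which the protocol would judge success and support a general-practice tool.

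**Working it through.** **Timing.** The imputation window after baseline is 12 months. It covers all of the 1-, 3- and 6-month and 1-year prediction windows, 1/5 = 20% of the 5-year window and 1/10 = 10% of the 10-year window. The short horizons are therefore the most exposed.

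**Scope.** The Missing data section states one procedure. No section sets a different one for the GOLD test sample or AURUM, or says how a gap would be filled for one patient at the point of use.

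**Size.** The plan gives no figure on this point, so the size was illustrated by simulation. All inputs are assumptions except the 80:20 split and the 40% limit:
- 200 000 patients; standardised age (complete) and one covariate x (incomplete), correlation 0.3.
- Logistic outcome: log-odds = −4.6 + 0.8·age + 0.6·x.
- A later measure of x for every patient, correlated 0.7 with x. It is either unaffected by AF or shifted by 0.5 SD in those who develop AF.
- x missing at random in 20% or 40%, filled by normal regression with a random residual. Test-set AUC is averaged over 4 replicates of 3 draws each.

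| Imputation model for x | Fitted on | 20% missing | 40% missing |
|---|---|---|---|
| Baseline information only | training | 0.7692 | 0.7586 |
| Baseline information only | all data | 0.7685 | 0.7587 |
| Plus later measure, unaffected by AF | training | 0.7738 | 0.7670 |
| Plus later measure, unaffected by AF | all data | 0.7744 | 0.7681 |
| Plus later measure, shifted by AF | training | 0.7813 | 0.7813 |
| Plus later measure, shifted by AF | all data | 0.7820 | 0.7825 |

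Effect of the later measure, fitted on training data only:
- 20% missing: 0.7738 − 0.7692 = 0.0046 (unaffected); 0.7813 − 0.7692 = 0.0121 (shifted).
- 40% missing: 0.7670 − 0.7586 = 0.0084 (unaffected); 0.7813 − 0.7586 = 0.0227 (shifted).

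Effect of fitting on all data instead of training data: between −0.0007 (0.7685 − 0.7692) and +0.0012 (0.7825 − 0.7813), which is negligible.

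**Scale.** Success is defined as a gain of at least 5% in accuracy over existing models. If that is read as relative AUC (an assumption) against the 0.827 quoted in the Introduction, the margin is 0.05 × 0.827 = 0.0414. At 40% missing the artefact would be 0.0084/0.0414 = 20% to 0.0227/0.0414 = 55% of it. At 20% missing it would be 0.0046/0.0414 = 11% to 0.0121/0.0414 = 29%.

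**The case against.** A reader might infer more than the text supports, in four ways.

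- **That data are imputed first and split afterwards.** The split acts on preprocessed data, but the description of preprocessing lists only recoding and code mapping. The Software section names imputation as its own step: "including data preprocessing, missing data imputation, model development and validation". The order is not stated, and in the simulation it hardly matters.
- **That the outcome is in the imputation model.** In the same simulation this gives 0.7807 and 0.7797 at 20% and 40% missing, gains of 0.0115 and 0.0211 over baseline information only. The text names the auxiliary inputs and does not mention the outcome, so these gains cannot be charged to the plan. Nor can a loss from unaveraged single draws, which the plan does not propose.
- **That multiple imputation cannot be used for one patient.** Fitted equations can be frozen and predictions averaged over draws. The obstacle is the input from the future, not the method.
- **That a measured/not-measured indicator is missing from the plan.** Nothing in the text excludes such information, and adding one is a matter of preference.

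It can also be said that an article leaves imputation detail to a fuller document. That holds for the order and the pooling, but not for the post-baseline inputs, which this article states and a fuller document would have to reverse.

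Other limits stand. Median imputation could be applied to a single patient, but it is planned only as a robustness check. A model built on diagnosis codes and age, such as the planned Transformer, may not use the imputed measurements at all. Comparators refitted on the same imputed data would share the bias, so it matters most against published figures.

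**Conclusion.** The concern holds in a limited form. As written, imputed baseline values in the GOLD test sample and AURUM can draw on measures from the following year, so the reported performance is not that of prospective use. The direction is optimistic. On the assumed inputs the AUC gain is about 0.005–0.012 at 20% missing and 0.008–0.023 at 40%. The upper ends require the later measure to be shifted by AF, which is most plausible for horizons up to one year.

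The simulation probably errs on the high side. Its baseline-only model uses age alone, without the earlier measures the plan also has. It gives every patient a later measure. It also scores single draws, and averaging predictions could narrow the gaps. The size is therefore uncertain, but the use of future information is stated in the text. This should be corrected before validation. It does not invalidate the study design.

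**What to change.** State in the Missing data section that, for any data used to evaluate prediction:
- the imputation model uses only information available at or before baseline, and excludes the outcome and all post-baseline measures;
- it is fitted on the GOLD training sample, frozen, and applied unchanged to the GOLD test sample and AURUM;
- if multiple imputation is kept, predictions are averaged over draws;
- performance under this procedure is the main reported result.

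Multiple imputation with the fuller set of inputs may stay for quantifying risk markers or as a sensitivity analysis, labelled as such.

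The cost is mainly plan wording. Some imputed values will be less accurate without the later measures, and the reported AUC may be slightly lower.
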